### Other information

The following information will be collected during the baseline interviews to conduct sub-group analyses and to identify factors associated with savings for maternal healthcare and male involvement during pregnancy: age, education, employment, area of residence (rural or urban), pregnancy intention, joint decision making within a couple. Other information, such as feedback on the intervention, will be collected to inform future interventions, but this information will not be part of the analysis for this study.

### Data collection

On the day of enrollment after consenting to join the study, all participants will fill out an interviewer-administered survey conducted by research assistants to identify baseline characteristics, demographic information, savings intention and behavior, and knowledge of and involvement in maternal health. This information will be used to conduct descriptive statistics and sub-group analyses to identify factors associated with savings behavior: age, education, marital status, employment, rural/ urban status, estimated wealth quintile, pregnancy status, attitudes towards male involvement in pregnancy, attitudes of and behaviors towards saving money, pregnancy preparation intentions.

Once a woman delivers, data on the amount saved plus any expenditures during the period of the intervention will be pulled from clinicPesa’s database for registered participants [46, 47]. The participants will also be called for an end-line questionnaire two weeks after their estimated delivery date that collects the same information as baseline with additional items on how they used the clinicPesa platform, delivery experience, and perceived involvement of the male partner in maternal healthcare. A pre-test of the data collection tools will be conducted with 14 random participants users from clinicPesa’s user base.

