### Data analysis

Background characteristics will be analyzed to determine that both the control and intervention groups were balanced and randomization was done correctly. The primary outcome of birth preparedness and maternal health utilization will be compared between the intervention and control groups. The mean total savings amounts of participants (regardless of expenditure) will be compared between the intervention and the control groups using T-tests for mean savings. Mixed-effect regression analysis will be performed to assess the effect of the intervention on the following outcomes: amount of money saved across the study period (plus withdrawals), birth preparedness, maternal health service utilization, male involvement in maternal healthcare, and utilization of money for pregnancy-related health costs (delivery, preparation, transportation, or other, if applicable). Logistic regression will be used to control for potential cluster effects. Weighting approach will be used to control for variation in probability of participants being included in the study across study recruitment sites (large facilities vs small facilities).

It is expected that after a participant enrolls in the study and is randomized, final savings data can be collected remotely even if the participant does not engage with the platform (i.e., does not save any money after enrollment) or complete the end-line survey. In this case, savings outcome data can still be collected. Attrition rates and reasons for dropout will be logged if possible. An intention to treat (ITT) analysis will be conducted, and a sensitivity analysis will be conducted for any missing data [48, 49]. The significance level will be set at 5%, and Stata version 13.1 will be used for analysis of the data set.

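### Savings are compared by an unadjusted t-test and by a mixed-effect model with neither named as main, and no sentence uses the pre-allocation baseline survey to estimate the intervention effect

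*Protocol article*

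**What the plan says.** **Baseline data.** Under Data collection, on the day of enrollment "all participants will fill out an interviewer-administered survey conducted by research assistants to identify baseline characteristics". The variables listed there include estimated wealth quintile and "attitudes of and behaviors towards saving money, pregnancy preparation intentions". Their use is then given: "This information will be used to conduct descriptive statistics and sub-group analyses to identify factors associated with savings behavior". The end-line questionnaire "collects the same information as baseline with additional items on how they used the clinicPesa platform". The Other information section describes a partly different list (age, education, employment, residence, pregnancy intention, joint decision making), "collected during the baseline interviews to conduct sub-group analyses and to identify factors associated with savings for maternal healthcare and male involvement during pregnancy".

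**Analysis.** The Data analysis section gives baseline data one further use: "Background characteristics will be analyzed to determine that both the control and intervention groups were balanced and randomization was done correctly". Mean total savings "will be compared between the intervention and the control groups using T-tests for mean savings". For the primary outcome it says: "The primary outcome of birth preparedness and maternal health utilization will be compared between the intervention and control groups", with no method in that sentence. It then plans mixed-effect regression for the effect of the intervention on five outcomes, among them money saved, birth preparedness and service utilization. It names no fixed-effect covariates for that model. The adjustments it does name are for cluster effects and, by weighting, for unequal inclusion probability across recruitment sites.

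**The concern.** Two things are left loose. First, total savings has two analyses, and nothing says which one gives the headline result. Secondly, the trial gathers likely predictors of saving from everyone before allocation, and each stated use of them lies outside the estimate of the intervention effect.

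If the t-test is the main savings result, all variation in savings that household means or saving habit could explain stays in the error term. The interval is then wider than the same data allow. A chance difference between arms in wealth or saving habit also passes into the estimate: the balance check could show it, but no step is attached to what it finds.

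**Working it through.** **1. Are the baseline answers safe to adjust for?** The survey is taken on the day of enrollment (Data collection). Allocation is matched at the end of each recruiting day (Randomization). The answers therefore precede allocation and can enter a regression without harm.

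**2. What is stated about adjustment, by outcome?**

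| Outcome | Stated test | Planned model | Baseline covariates |
|---|---|---|---|
| Total savings (secondary) | t-test, unadjusted | Mixed-effect regression | Not listed, not excluded |
| Birth preparedness and service use (primary) | Compared, no method in that sentence | Mixed-effect regression | Not listed, not excluded |

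Only the savings t-test is unadjusted by statement.

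**3. The plan's own sample size.** Inputs from the sample size section: 80% power, 5% significance, 286 per arm, 350 per arm recruited, about 20% dropout. The event rates and effect are not given there, so 286 can be neither confirmed nor refuted; for example, 50% versus 61.6% gives 287 per arm without continuity correction. On the 700: 572/0.8 = 715 and 572 × 1.2 = 686.4, so 700 is within about 3% of either method.

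**4. Translation to a continuous outcome (assumption, two-sided 5%).** The standardized difference with 80% power at 286 per arm is

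d = (1.960 + 0.842) × √(2/286) = 0.234.

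This is a yardstick. The trial was sized on service utilization, not on savings.

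**5. Power with adjustment.** With rho the correlation between the baseline covariates and the outcome,

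power = Φ( d × √(n/2) / √(1 − rho²) − 1.960 ).

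At n = 286, d × √143 = 2.802. For rho 0.3, 2.802/0.954 − 1.960 = 0.977, and Φ = 83.6%. The article gives no rho, so a range is shown:

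| rho (assumed) | Standard error × | Power, 286 per arm | Power, 350 per arm |
|---|---|---|---|
| 0 | 1.000 | 80.0% | 87.3% |
| 0.1 | 0.995 | 80.4% | 87.6% |
| 0.2 | 0.980 | 81.6% | 88.6% |
| 0.3 | 0.954 | 83.6% | 90.1% |
| 0.4 | 0.917 | 86.4% | 92.2% |
| 0.5 | 0.866 | 89.9% | 94.7% |

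The 350 column matters for savings, because the article expects account data even from participants who do not complete the end-line survey. A gain of 5 points needs rho of about 0.35 at 286 per arm and about 0.40 at 350. For survey outcomes, exactly 20% loss from 350 leaves 280 per arm, where unadjusted power for the same d is 79.2%.

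**6. Chance imbalance.** At 350 per arm, the standard error of a baseline difference in SD units is √(2/350) = 0.0756. The chance of a difference beyond 0.1 SD in a given continuous covariate is 2 × Φ(−0.1/0.0756) = about 19%. At an assumed rho of 0.4, such a difference moves the estimate by 0.4 × 0.1 = 0.04 SD, which is 0.04/0.234 = 17% of the yardstick difference.

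**The case against.** The strongest reply is that adjustment is not ruled out. A mixed-effect regression is planned for savings and for birth preparedness alike, and its covariate list is the kind of detail that an article leaves to the full protocol or SAP. The statement of use under Data collection does not claim to be complete; the balance check is a use that it omits. This stands. A reader might infer that baseline data are reserved for description and sub-groups, and that the primary outcome will be analyzed without adjustment. The article says neither.

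A reader might also take the Other information section as a second statement confining these same variables to sub-group work. It does not list wealth quintile, saving behavior or preparation intentions, so it is no evidence for them.

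Next, the prognostic strength is unknown. Account savings are counted from enrollment, so the survey items are proxies and not earlier values of the outcome. The article allows that money may be saved elsewhere and that some participants may save nothing. Rho could be small, and at 0.1 to 0.2 the gain is 0.4 to 1.6 points. This also stands, and is why the range above starts low.

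Last, an unadjusted comparison is valid under randomization. That is correct, and it limits the point to efficiency. It does not answer the remaining gap: two analyses of savings with no ranking, and no stated role for baseline data in either.

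**Conclusion.** The point holds in limited form, most firmly for savings. An unadjusted t-test and a mixed-effect regression stand side by side with no main analysis named, and no sentence uses the pre-allocation survey to estimate the effect. For birth preparedness and service use, lack of adjustment would be an inference; there the point is only that the article should say what enters the model.

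What is at stake is precision, with no bias on average and no inflation of type I error. For a continuous outcome at 286 per arm the gain runs from 0.4 points of power (rho 0.1) to 9.9 points (rho 0.5). This rests on an assumed rho, a two-sided 5% test and a standardized difference carried over from a calculation for another outcome. Gains are smaller for binary items such as facility delivery and skilled attendance. It is a worthwhile, inexpensive improvement and not a flaw that threatens validity.

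**What to change.** In Data analysis:

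- Name the planned regression as the main comparison of total savings, with a small fixed set of baseline covariates: baseline saving behavior and wealth quintile. Keep the t-test as a supporting unadjusted result.
- In the planned regression for birth preparedness and service use, enter wealth quintile and baseline pregnancy-preparation intention. Report marginal (standardized) differences for binary items, so that the adjusted result is not only a conditional odds ratio.
- State that these covariates are fixed before the outcome analysis begins, and so before unblinding, and are included whatever the balance check shows.

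In Data collection, add covariate adjustment of the arm comparisons to the stated uses of the baseline survey.

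The cost is a few sentences, with no new data, visits or participants. The downsides are small: a few missing baseline answers will need simple imputation, and the headline savings estimate becomes an adjusted one with the unadjusted result beside it. If rho proves low, a few pre-named covariates cost almost nothing with several hundred participants per arm.

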### Data analysis

Background characteristics will be analyzed to determine that both the control and intervention groups were balanced and randomization was done correctly. The primary outcome of birth preparedness and maternal health utilization will be compared between the intervention and control groups. The mean total savings amounts of participants (regardless of expenditure) will be compared between the intervention and the control groups using T-tests for mean savings. Mixed-effect regression analysis will be performed to assess the effect of the intervention on the following outcomes: amount of money saved across the study period (plus withdrawals), birth preparedness, maternal health service utilization, male involvement in maternal healthcare, and utilization of money for pregnancy-related health costs (delivery, preparation, transportation, or other, if applicable). Logistic regression will be used to control for potential cluster effects. Weighting approach will be used to control for variation in probability of participants being included in the study across study recruitment sites (large facilities vs small facilities).

It is expected that after a participant enrolls in the study and is randomized, final savings data can be collected remotely even if the participant does not engage with the platform (i.e., does not save any money after enrollment) or complete the end-line survey. In this case, savings outcome data can still be collected. Attrition rates and reasons for dropout will be logged if possible. An intention to treat (ITT) analysis will be conducted, and a sensitivity analysis will be conducted for any missing data [48, 49]. The significance level will be set at 5%, and Stata version 13.1 will be used for analysis of the data set.

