**Methods:**

A randomized controlled trial will be conducted to assess the effectiveness of the intervention among pregnant women or their partners in Uganda’s central region, including the capital of Kampala. Seven hundred pregnant women (12–35 gestational weeks) or their partners will be recruited. All participants will receive access to a committed mobile money health savings account provided by a local organization that also offers savings targets and reminders for antenatal care appointments and health tips as part of a “Mamas Program” offered to expectant mothers. The time period in the intervention is from the day of enrollment until two weeks after the delivery date. The control group will receive the standard Mama Program offering. The intervention group will receive the standard Mama Program offering plus behavioral designs encouraging savings behavior through short-message service (SMS) text messages. The primary outcome is usage of maternal health services measured by level of birth preparedness and delivery at a health facility. Secondary outcomes include male involvement in maternal healthcare, measured by financial support, as well as total savings for healthcare, assessed using the validated amount of savings accrued in participants’ clinicPesa accounts from the day of enrollment plus any withdrawals for healthcare expenditures during the intervention period.

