### Sample size, eligibility, and recruitment

The minimum sample size for the RCT is 572 participants (286 in each arm). It was calculated using OpenEpi version 3. The power of the study was set at 80% and the significance level at 5%. A previous savings group research in a SSA region for maternal healthcare service utilization was used for assumptions [43]. Considering an approximate 20% dropout rate and sampling unit rounding, 700 participants will be recruited (350 participants in each arm).

To be eligible for joining in this study, participants should have the following characteristics: (1) 18–49 years old, (2) between 12–35 gestational weeks (pregnant female) OR partner of someone who is (male), (3) own a mobile phone, (4) has a registered Mobile Telephone Network (MTN) mobile money account, (5) willingness to enroll in clinicPesa’s health savings mobile money account. Participants are ineligible if their partner is known to already be participating in the study to avoid duplicating results of savings amounts; only one member per household may participate in the study.

Participants will be recruited and enrolled in person by clinicPesa at 77 public and private health facilities where clinicPesa operates. Five trained research assistants will approach male and female clients at the maternity ward of selected health facilities. The clients at the health facility will be offered an opportunity to enroll in the study when they sign up to join clinicPesa. In the case of a COVID-19 lockdown on movement, participants will be recruited through a phone query from clinicPesa’s registered user base. Users who sign up for clinicPesa agree to terms and conditions set by clinicPesa, which include the possibility of being offered to join studies to improve the product offered by clinicPesa.

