### Outcomes

The primary outcome is level of birth preparedness and usage of maternal health services, assessed by the number of birth kits or items within birth kits purchased, antenatal care visits, skilled birth attendance by a doctor, nurse, midwife, and/or medical assistant or clinical officer, and delivery at a health facility, all based on recall by the participant; the amount of validated expenditure in participants’ clinicPesa accounts from the day of enrollment during the intervention period will also be assessed. The primary outcome will be measured by asking the participant during the end-line survey about their pregnancy and delivery experience.

Secondary outcomes include male involvement in maternal healthcare, measured by financial support, attendance to ANC, assisting with planning the delivery, and providing perceived emotional support to the mother, as well as total savings for healthcare, assessed using the validated amount of savings accrued in participants’ clinicPesa accounts from the day of enrollment plus any withdrawals for healthcare expenditures during the intervention period. The withdrawals will also be coded to determine if they were used for maternal health service costs, including transport, or other healthcare costs, such as birth preparedness kits, baby materials, or others. Deposits into the account will be coded by whether it was the mobile money account owner or another mobile money account (for example, a different family member saving into the account).

Male involvement in maternal healthcare will be assessed by measuring whether they provided financial support for clinicPesa or otherwise, attendance to ANC, and assisting with planning of the delivery, measured by an ad-hoc male involvement index [45]. Women will be queried about the perceived levels of involvement, and men will be queried about their level of involvement.

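### Time available to save varies about four-fold with gestational age at entry, yet no analysis names that covariate, and antenatal visits and birth-kit items have no counting start date

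*Protocol article*

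**What the plan says.** Eligibility (Sample size, eligibility, and recruitment) admits women at 12 to 35 gestational weeks, or the male partner of such a woman. The abstract fixes the follow-up: "The time period in the intervention is from the day of enrollment until two weeks after the delivery date". In the Outcomes section, total savings are the amounts accrued in participants' clinicPesa "accounts from the day of enrollment plus any withdrawals for healthcare expenditures during the intervention period", so the outcome is cumulative from entry.

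The Data analysis section names two analyses of savings. Mean totals "will be compared between the intervention and the control groups using T-tests for mean savings". Then: "Mixed-effect regression analysis will be performed to assess the effect of the intervention on the following outcomes: amount of money saved across the study period", with withdrawals added back. The same regression is to cover "birth preparedness, maternal health service utilization, male involvement in maternal healthcare, and utilization of money for pregnancy-related health costs". No covariates are listed for it, and neither savings analysis is called the main one. Gestational age at entry and time in the study appear in neither analysis. The Randomization section describes 1:1 allocation of individuals and mentions no stratification by gestational age.

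For the primary outcome, the Outcomes section lists birth kits or kit items purchased, antenatal visits, skilled attendance and facility delivery, all by recall, plus account expenditure dated from enrolment. It adds: "The primary outcome will be measured by asking the participant during the end-line survey about their pregnancy and delivery experience". No start date is given for the visit and kit counts.

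**The concern.** How much a participant can save depends on how many weeks remain, and that is fixed at entry by gestational age. An unadjusted comparison leaves this known baseline variation in the error term. It also lets a chance difference between arms in gestational age pass into the point estimate. The variable is established at screening, so using it costs nothing.

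The second issue is the counting window. Visits made and items bought before randomization cannot be changed by the messages. If they are counted, the expected difference in mean counts is unchanged, because randomization balances earlier events. The relative effect shrinks, however, and variation in earlier events enters the comparison. If earlier events are not recorded separately at baseline, no later analysis plan can separate them reliably.

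**Working it through.** The article gives no distribution of entry weeks and no standard deviation of savings, so there is no stated figure to reproduce. Every size below rests on the assumptions shown.

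1. **Exposure.** Inputs: entry at 12 to 35 weeks (eligibility) and an end two weeks after delivery (abstract). Assumption: delivery at 40 weeks. Weeks = 40 + 2 − entry week.
   - Entry at 12: 30 weeks. Entry at 35: 7 weeks. Ratio 30/7 = 4.3.
   - Delivery at 39, 41 or 42 weeks: 29/6 = 4.8, 31/8 = 3.9, 32/9 = 3.6.
   - Counted only to delivery: 28/5 = 5.6.

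2. **Spread of exposure.** Assume entry uniform over the allowed range, so exposure is uniform on 7 to 30 weeks. Mean = (7 + 30)/2 = 18.5. SD = (30 − 7)/√12 = 6.64. Coefficient of variation (CV) = 6.64/18.5 = 0.359, squared 0.1288.

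3. **Precision.** Assume total savings = weekly rate × weeks, with the two independent. Then CV²(total) = (1 + CV²rate)(1 + 0.1288) − 1, and the share of variance explained by weeks is R² = 0.1288/CV²(total). The equivalent gain in participants is 1/(1 − R²). Where the unadjusted test has 80% power at two-sided 5%, adjusted power is approximately Φ[(1.960 + 0.842)/√(1 − R²) − 1.960].

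| Weekly-rate CV (assumed) | CV²(total) | R² | 1/(1 − R²) | Power, from 80% |
|---|---|---|---|---|
| 0.5 | 0.411 | 31% | 1.46 | 92% |
| 1 | 1.258 | 10% | 1.11 | 84% |
| 2 | 4.644 | 3% | 1.03 | 81% |
| 3 | 10.288 | 1% | 1.01 | 80.5% |

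4. **Validity.** Simulation with 286 per arm, log-normal weekly rates and 5,000 runs per setting, at CV 0.5, 1 and 2:
   - Type I error of the unadjusted t-test: 4.9%, 5.1% and 4.2%. Adjusted regression with robust standard errors: 4.6%, 4.6% and 4.4%.
   - Power with an effect proportional to savings, unadjusted to adjusted: 74% to 89%, 71% to 76%, 69% to 70%. These start below 80% because a proportional effect also raises the variance in the intervention arm. The pattern matches the table.

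5. **Chance imbalance.** SE of the between-arm difference in mean exposure = 6.64 × √(2/286) = 0.56 week, so 95% of trials lie within ±1.09 weeks (1.09/18.5 = 5.9% of the mean). With all 350 per arm: 0.50 week, ±0.98 weeks, 5.3%. The t-test's standard error already allows for this; adjustment would remove it.

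6. **Counting window.** Savings and account expenditure are dated from enrolment. Skilled attendance and facility delivery occur at the birth, after entry. Only antenatal visits and kit items have no start date. If they are counted over the pregnancy, the share of weeks 12 to 40 that precedes enrolment is (entry − 12)/28. This is 0% at entry week 12, 23/28 = 82% at week 35, and 11.5/28 = 41% on average (uniform entry, mean 23.5 weeks). These are shares of time, not of visits or purchases.

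**The case against.** Several stronger readings are tempting, and the document does not support them.

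- **That the t-test is the only savings analysis.** It is not. The next sentence plans a mixed-effect regression of savings and of the primary outcome. Its covariates may properly be left to an analysis plan that is not shown, so an unlisted covariate is not a defect by itself. What stands is that the article does fix an unadjusted t-test for savings and does not say which analysis leads.
- **That gestational age has been excluded from the model.** The baseline lists in the Other information and Data collection sections serve description, sub-groups and associated factors. They do not specify the treatment-effect model. Pregnancy status is listed and may record gestation, and the Intervention section ties some messages to time in the intervention. Absence from these lists proves nothing about the regression.
- **That unequal exposure biases the comparison.** Allocation is individual and 1:1, so exposure is balanced in expectation and the t-test keeps its error rate.
- **That visits and kits are counted over the whole pregnancy.** This is a likely reading of an end-line question about the pregnancy, not stated text. The questionnaires are not shown, and the baseline survey may already ask about visits or items to date.

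It is also fair that the larger precision gains need a low weekly-rate CV. Participants who save nothing, whom the Data analysis section anticipates, raise that CV. Savings set by targets need not grow in proportion to time. Total visits per pregnancy is in itself a legitimate outcome. These points limit the size of the concern. They do not remove the case for using a strong, freely available baseline covariate or for fixing the counting window.

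**Conclusion.** The point holds as a matter of precision and outcome definition, not of validity. Exposure ranges from about 30 to 7 weeks (4.3-fold at a 40-week term; 3.6 to 4.8 for delivery at 42 to 39 weeks). Gestational age at entry is named in neither savings analysis. The precision at stake is about 31%, 10%, 3% or 1% of savings variance at a weekly-rate CV of 0.5, 1, 2 or 3, given uniform entry and savings proportional to time. It may therefore be substantial or negligible, and the document does not allow a choice between these.

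Separately, the window for antenatal visits and birth-kit items is undefined. Events before randomization probably enter and dilute these two components of the primary outcome. Skilled attendance, facility delivery and account expenditure are unaffected. A reader might infer an inflated false-positive rate or a biased savings difference; neither follows.

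**What to change.** **Savings and other outcomes.** Make the already planned regression the main analysis of total savings in place of the t-test, with arm and gestational age at enrolment as covariates and robust standard errors. Use the same covariate for the other outcomes. Adjust for gestational age at entry and not for realised weeks, because the delivery date is known only after randomization. This needs a change of wording only: eligibility already requires gestational age, and the end-line call already requires an estimated delivery date.

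**Visits and kit items.** State the counting window. If the baseline questionnaire does not already do so, record antenatal visits to date and kit items already owned. Then either adjust the end-line count for the baseline count, or count from enrolment. A count from enrolment depends on entry week by construction, so it needs the gestational-age covariate as well.

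**Cost.** Two short baseline questions. Enrolment was expected to start in June 2022 and the article appeared in August 2022, so some participants may already have been recruited. They could be asked at end-line how many visits and purchases came before enrolment, with some recall error.

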### Randomization

A person who is not involved with any other study procedure (including recruitment, implementation of the intervention, and data analysis) will share a computer-generated randomized allocation table with clinicPesa at the beginning of the recruitment period, which will not be shared with the study recruitment team [44]. At the end of each recruiting day, the customer ID numbers of participants who agreed to join the study will be matched to the table to be assigned to either the control or the intervention group (1:1 randomization), and a study participant ID will be created to maintain participant anonymity within the study [32].

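### Cluster control is assigned to logistic regression with no cluster term named, and weighting for inclusion by facility would cost precision without removing bias from the randomized comparison

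*Protocol article*

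**What the plan says.** The Data analysis section of the protocol article gives three instructions that bear on recruitment site.

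- Mixed-effect regression is to estimate the intervention effect on savings, birth preparedness, service use, male involvement and pregnancy-related spending. The random-effect unit is not named. A t-test is also named for mean savings.
- On clustering, the section says: "Logistic regression will be used to control for potential cluster effects". It does not say what the cluster is.
- On unequal inclusion by site, it says: "Weighting approach will be used to control for variation in probability of participants being included in the study across study recruitment sites", with large and small facilities given as the contrast.

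Under Randomization, participants are matched to one computer-generated table and "assigned to either the control or the intervention group (1:1 randomization"). No stratification by facility is described. Under Sample size, eligibility, and recruitment, the partner company operates at 77 facilities and "Five trained research assistants will approach male and female clients at the maternity ward of selected health facilities". A phone query of the existing user base is the fallback during a lockdown. No sampling frame or sampling fraction appears. On size: "The minimum sample size for the RCT is 572 participants (286 in each arm"), at 80% power and a 5% significance level, and then "Considering an approximate 20% dropout rate and sampling unit rounding, 700 participants will be recruited (350 participants in each arm"). Dropout and rounding are the only allowances mentioned.

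**The concern.** Two statements claim a property that the named method does not have.

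First, logistic regression treats observations as independent given the covariates. It accounts for clustering only if something is added: site effects, GEE or a cluster-robust variance. Nothing is named, and neither is the cluster. Households are ruled out because only one member may join, so facility is the likely meaning. The mixed model's random effect could equally be the participant, since the end-line survey repeats the baseline items.

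Second, the weights are meant to control for unequal inclusion across sites. In an individually randomized trial with one allocation ratio, unequal inclusion does not confound the arm comparison, so there is no bias for the weights to remove. Unequal weights do raise the variance. If they enter the primary comparison, the trial has less power than its sample size implies. A reader also cannot tell whether the reported effect will come from a mixed model, a logistic model or a weighted version of either.

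**Working it through.** **The plan's own figure.** The 572 cannot be reproduced, because the article takes its assumptions from a cited study and gives no rates. For orientation only, at two-sided 5% (sidedness assumed) and 80% power, 286 per arm corresponds to, for example, 50% versus about 62%, or 70% versus about 80%. The inflation step is sound: 572/0.8 = 715 and 572 × 1.2 = 686.4, both within 3% of 700. With exactly 20% dropout, 700 × 0.8 = 560 remain, for 79.2% power, a trivial difference.

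**Does facility size confound the comparison?** With 1:1 allocation from one table, the probability of being in the intervention arm is 1/2 at every facility. A weight that depends only on facility is therefore independent of arm. If the effect is the same everywhere, weighted and unweighted analyses have the same target. If it varies, the unweighted analysis averages over those enrolled and the weighted one over a population defined by the weights. That is a change of estimand, not a correction of bias.

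**Cost of weighting.** The document gives no weights, so the ratios and mixes below are assumptions. The design effect is Kish's, E[w²]/(E[w])², for two weight classes. Power is Φ(2.80/√deff − 1.96), where 2.80 = 1.96 + 0.84 gives 80% at 572.

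Worked case, ratio 3:1 with half the sample in each class: E[w] = 2 and E[w²] = 5, so deff = 5/4 = 1.25. Effective N is 572/1.25 = 458. Power is Φ(2.80/1.118 − 1.96) = Φ(0.545) = 70.7%.

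| Weight ratio | deff (50% / 30% at the high weight) | Effective N | Power |
|---|---|---|---|
| 1.5:1 | 1.04 / 1.04 | 550 / 550 | 78.4% / 78.5% |
| 2:1 | 1.11 / 1.12 | 515 / 509 | 75.7% / 75.2% |
| 3:1 | 1.25 / 1.33 | 458 / 431 | 70.7% / 68.1% |
| 5:1 | 1.44 / 1.69 | 396 / 338 | 64.5% / 57.6% |

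In the worked case, restoring 80% needs 572 × 1.25 = 715 analysed, more than the 700 to be recruited, or 715/0.8 = 894 recruited.

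**Simulation.** Settings: 572 analysed, 77 sites of unequal size, individual randomization without site stratification, binary outcome, conditional log-odds ratio 0.5, 3,000 runs per setting. ICCs are assumed.

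| ICC | Type I error, plain logistic | Power, plain logistic | Power, weighted 3:1 / 5:1 |
|---|---|---|---|
| 0 | 5.4% | 78.9% | 68.7% / 61.1% |
| 0.05 | 4.7% | 77.6% | 67.0% / 60.1% |
| 0.15 | 5.4% | 70.3% | 60.8% / 54.6% |

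Weighted analyses used a sandwich variance and kept type I error at 4.9-5.5%. Weighting cost about 10 to 18 points, in line with the Kish figures. The fall in plain logistic power down the column compares settings with different site variation at a fixed conditional effect. It is not what a facility term would recover.

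**Gain from modelling facility.** For a linear outcome with m analysed per site and ICC r, under simple randomization, information relative to ignoring site is [(m − 1)/(1 − r) + 1/(1 + (m − 1)r)]/m. With 77 equal sites, m = 572/77 ≈ 7.4.

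- r = 0.05: [6.4/0.95 + 1/1.32]/7.4 = 1.013, so power = Φ(2.80 × √1.013 − 1.96) ≈ 80.5%.
- r = 0.10: [6.4/0.90 + 1/1.64]/7.4 = 1.043, so power ≈ 81.6%.

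One assumed skewed distribution of site sizes gives 80.7% and 82.1%. If only 20 equal sites recruit, the figures are 81.2% and 83.0%.

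**The case against.** The strongest reply is that the sentence just before the logistic one already names mixed-effect regression for the listed outcomes. A mixed model can carry a facility effect, and the two sentences together may be a compressed description of mixed-effects logistic regression for binary outcomes. The random-effect unit and the link are details that an article may leave to an analysis plan. This stands in part. A reader might infer that site is handled only by plain logistic regression, and the text does not support that. What remains is that cluster control is explicitly attached to a method that does not provide it.

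Other stronger readings also fail:

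- *Ignoring site invalidates the test.* It does not under individual randomization, as the simulated type I error shows.
- *Logistic regression is misapplied to savings or counts.* The article never assigns it to them. Savings go to a t-test and mixed-effect regression.
- *Inclusion probabilities cannot be known.* The article describes no fractions, and approaching clients at selected sites with a phone fallback makes true probabilities hard to obtain. Approximate weights from facility volume are not ruled out.
- *Modelling facility yields a large gain in power.* That would require arms balanced within sites, and no site stratification is described.

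The other side can also say that weights could serve a facility-population average effect. That is legitimate, but the article states no such estimand. Finally, it does not say which analyses will be weighted, so weighting of the primary comparison is a possibility and not a stated fact.

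**Conclusion.** The concern holds in a limited form, and the text should be changed. The logistic sentence is wrong as written, but its practical consequence is modest: type I error stays near 5%, and a facility term adds about 0.5 to 2 points of power with 77 sites at ICC 0.05-0.10.

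The weighting sentence matters more. Followed for the primary comparison, it loses precision with no gain in internal validity. The size depends wholly on weights that the article does not give: about 1.5 points at 1.5:1, 4 to 5 at 2:1, 9 to 12 at 3:1 and 15 to 22 at 5:1. These figures assume two weight classes with 30% or 50% of the sample at the higher weight, 572 analysed and a nominal 80% power. They illustrate exposure and do not predict this trial's power.

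**What to change.** Replace the logistic and weighting sentences with one statement. For each outcome, the primary analysis is an unweighted intention-to-treat mixed-effects model with recruitment facility as the named random intercept. The link suits the outcome: logistic for binary outcomes, a count model for counts and linear for amounts. Say which facility code phone-recruited participants receive. Keep facility-size weighting only as a sensitivity analysis, and define the source of the weights and the population they represent.

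The cost is a few lines of text and no extra data or recruitment, and it is best done before outcomes are analysed. There are two downsides. The main estimate is not re-weighted to a facility population. The logistic mixed model also gives a facility-conditional odds ratio, which should be labelled as such.
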